### Trial design

This is a multicentre, randomized, double-blind, two arm pilot study, with a balanced (1:1) allocation that will be carried out in the level III neonatal intensive care units in 2 centres in Ireland: The Rotunda Hospital Dublin and Cork University Maternity Hospital, and one centre in the Netherlands: Radboudumc Amalia Children’s Hospital, Nijmegen (Fig. 1).

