### The relevance of the primary outcome

iNO use is expensive and currently requires invasive ventilation. Invasive ventilation can cause baro- and volutrauma, may lead to parenchymal lung damage and the evolution of pneumothoraces. Ventilation is often accompanied by the administration of sedative agents such as morphine and midazolam. In addition, prolonged ventilation will delay bonding with parents, delay feeding and suckling and will lead to prolonged hospitalisation. A reduction in the time spent invasively ventilated will (in addition to the other benefits outlined above) reduce hospital stay, promote earlier enteral nutrition, parental bonding, breast feeding and significantly reduce healthcare costs.

The purpose of this pilot study is to assess the feasibility of performing a pivotal trial and to obtain preliminary data to calculate a sample size for a definitive multi-centre trial of milrinone therapy in PPHN. We aim to recruit a total of 20 infants with PPHN (10 receiving milrinone and 10 receiving placebo) over a 4-year period. We then plan to seek additional funding in order to facilitate the running of the multicentre RCT in European and North American centres. In this pilot study we also aim to ascertain issues with recruiting infants and obtaining consent, compliance with the protocol, the rate (if any) of loss to follow up, and the general acceptability, feasibility and compliance of administering the intervention. This number will also allow us to calculate a standard deviation which will be used in a sample size calculation for the full-scale trial. In addition, we aim to refine the criteria for discontinuing therapy which are outlined below.

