#### Monitoring, outcome measures and participant timeline

The primary outcome of this study is the time on iNO in hours and the time on invasive ventilation. A standardised protocol for iNO weaning is detailed in Additional file 2.

We will collect the following demographic characteristics and relevant short-term secondary outcomes: duration of hospital stay; time to extubation; duration of oxygen therapy, and survival.

**Details of cardiorespiratory stability** (blood pressure, heart rate, oxygen saturation), ventilation support (FiO_2_, mean airway pressure (MAP), oxygenation index [MAP × F FiO_2_/PaO_2_]), efficacy of oxygenation [PaO_2_], plasma lactate, pH, PCO_2_, HCO_3_^−^, Base excess; and relevant co-treatments (i.e., sedation, analgesics, muscle relaxants, inotropes, fluid administration) at the following time points:Prior to treatmentFollowing the loading dose12 h after initiation of therapy24 h after initiation of therapyTwo hours after discontinuation of therapy

**Monitoring of blood parameters** will be carried out as follows during the study period and 24 h after drug discontinuation:Full blood count (including platelets): dailyElectrolytes, Urea and Creatinine: dailyLiver function tests (ALT, AST, GGT): dailyBlood gas analysis: 12 hourly

**Echocardiography** will be performed according to the following schedule: a timing window of ±3 h will be applied. Scans performed outside the ±3 h window will constitute a protocol deviation:Prior to the Commencement of Study Drug: Diagnose PPHN and rule out CHD12 h following the administration of Study Drug24 h following the administration of the study drug8 h following the discontinuation of the study drug

**Non-invasive Cardiac output Monitoring (NICOM)** will be commenced prior to the commencement of the study drug and continued until the last echocardiogram, 8 h after the discontinuation of the study medication.

**Cranial ultrasound** will performed prior to treatment commencement and after the discontinuation of the infusion. Intraventricular haemorrhage will be defined and graded with the Papile classification [30]. Echocardiography will be carried out at baseline as detailed above and at 12 h, 24 h, 2 h after discontinuation of therapy, and before discharge.

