#### Echocardiography assessment of PPHN

All infants will undergo a comprehensive echocardiography assessment at baseline prior to enrollment to rule out congenital heart disease, quantify the magnitude of pulmonary hypertension and assess left and right ventricular output and function. The functional protocol for the echocardiography assessment is adapted from the recent American Society of Echocardiography Guideline on neonatal echocardiography [31, 32]. All infants will be assessed once established on iNO and are in a quiet state using the Vivid E9 or the Vivid S6 (GE Medical, Milwaukee, WI, USA) and a 10 Mhz transducer. A diagnosis of PPHN will be made if any of the following is identified in the absence of cyanotic congenital heart disease:A tricuspid regurgitant jet with a pressure gradient ≥^2^/_3_ systemic systolic blood pressureIntra-ventricular septum flattening or bowing into the left ventricular cavityPatent ductus arteriosus bidirectional shunting or predominant right to left shuntingA pulmonary artery acceleration time < 40 milliseconds

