### Data management and statistical analysis

#### Sample size

This study is conducted to determine the feasibility of patient recruitment, instituting the study protocol, randomising and blinding allocation, collecting outcome data and contribute to determine the sample size necessary for a definitive multicentre trial. A sample of 10 infants per arm (a total of 20 infants) will be recruited over a 4-year period.

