#### Statistical methods

The HRB IP CTN clinical trial statistician will conduct all the statistical analyses. The primary outcome and most of the secondary outcomes are continuous variables. Continuous variables will be tested for normality by comparing the mean and median, a histogram representation of data, and the Shapiro-Wilk test for normality and will be presented as means (standard deviation) or median [inter-quartile range] as appropriate. Dichotomous variables will be presented as proportions and summarised in contingency tables. The *primary analysis of the primary outcome* will be performed using an independent t-test (or a Wilcoxon Rank Sum test as appropriate) to compare the difference in time on iNO and invasive ventilation between the two groups. A chi squared test (or Fisher’s exact test) will be used for the *primary analysis of the dichotomous secondary* outcomes. For the continuous secondary outcomes, a t-test will be used to compare normally distributed data, and Wilcoxon Rank Sum test will be used for skewed data. We will accept a *p* value of < 0.05 as significant. We will use SPSS (version 22) to perform the statistical analysis.

All enrolled infants will be analysed on an intention-to-treat basis, including infants that have not continued treatment for any reason. Analysis for the feasibility study will only be conducted once the recruitment of all patients is completed. No interim analysis of treatment effect will be conducted. We anticipate that recruitment will take 4 years to complete with an additional 6 months required for the measurement of the echocardiography data and statistical analysis.

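### Continuous secondary measures with a pre-treatment value are assigned a plain two-group test; with 10 infants per arm, adjusting for baseline would usually be more precise

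*Protocol article*

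**What the plan says.** The Statistical methods section gives one rule for all continuous secondary outcomes: "For the continuous secondary outcomes, a t-test will be used to compare normally distributed data". Skewed measures go to a rank sum test instead. The section adds a p "value of < 0.05 as significant" and says that most secondary outcomes are continuous. Neither that section nor any other mentions a baseline covariate, a change score or a repeated-measures model.

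Pre-treatment values are nevertheless collected. Monitoring, outcome measures and participant timeline schedules blood pressure, heart rate, FiO2, oxygenation index (OI), PaO2 and lactate before treatment, after loading, at 12 h, at 24 h and after stopping. The first echocardiogram on that schedule is listed as "Prior to the Commencement of Study Drug: Diagnose PPHN and rule out CHD", and NICOM starts before study drug. Echocardiography assessment of PPHN adds: "All infants will undergo a comprehensive echocardiography assessment at baseline prior to enrollment". The functional parameters are then repeated at the scheduled times.

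The same monitoring section also names its short-term secondary outcomes: length of stay, time until extubation, time on oxygen, and survival. None of these has a baseline value.

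**The concern.** The haemodynamic and oxygenation measures are meant for comparing the arms. The Secondary objective includes ventricular function and output by echocardiography and NICOM, and the Conclusion says that these data will bear on the efficacy of milrinone. If they are compared by a two-group test that ignores the pre-treatment value, variation between infants that was already present before study drug stays in the error term.

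The trial is a "two arm pilot study, with a balanced (1:1) allocation", and its size is fixed: "A sample of 10 infants per arm (a total of 20 infants) will be recruited over a 4-year period". With so few infants and such slow recruitment, unused information is costly. What is at stake is the width of the confidence intervals for the mechanistic measures, and how far a chance difference at baseline carries into a result.

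**Working it through.** The article gives no power, effect size, SD or correlation for these measures, so it has no figure to reproduce.

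**Inputs.** From the article: 10 per arm (Sample size), 1:1 allocation (Trial design), significance level 0.05 (Statistical methods). Assumed: two-sided testing; normal data; equal SDs at baseline and follow-up; a linear relation with correlation ρ, shown as a range.

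**Chance imbalance.** The standard error of the difference in baseline means is √(2/10) = 0.447 SD. The chance of a difference above 0.5 SD in either direction is P(|Z| > 0.5/0.447 = 1.118) = 0.26 per measure. For scale, the group's earlier 11-infant study reports an OI of 41.6 ± 21.6 just before milrinone. With that SD, half an SD is 10.8 OI points. In an unadjusted comparison of on-treatment values, the expected carry-over is ρ times the imbalance. A 0.5 SD imbalance therefore shifts the difference by 0.15 SD at ρ = 0.3 and by 0.25 SD at ρ = 0.5.

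**Variance relative to a t-test on on-treatment values (N = 20).**
- ANCOVA: (1 − ρ²) × (1 + 1/(N − 4)) = (1 − ρ²) × 1.0625. The second factor is the cost of estimating one slope.
- Change-score t-test: 2(1 − ρ).
- Confidence interval width, ANCOVA to t-test: √(variance ratio) × 2.10982/2.10092 (t quantiles on 17 and 18 df).
- Equivalent size of an unadjusted trial: 20 / variance ratio.

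| ρ | ANCOVA variance ratio | Change-score variance ratio | ANCOVA CI width ratio | Equivalent N |
|---|---|---|---|---|
| 0 | 1.06 | 2.00 | 1.035 | 18.8 |
| 0.3 | 0.97 | 1.40 | 0.987 | 20.7 |
| 0.5 | 0.80 | 1.00 | 0.896 | 25.1 |
| 0.7 | 0.54 | 0.60 | 0.739 | 36.9 |
| 0.8 | 0.38 | 0.40 | 0.621 | 52.3 |

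**Break-even.** Setting (1 − ρ²) × 1.0625 = 1 gives ρ = √(1 − 1/1.0625) = 0.24. On interval width the break-even is 0.26. Below about 0.25 adjustment does not help.

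**Power, as an illustration only.** For a true difference of 1 SD (noncentral t), the unadjusted t-test has power 0.56. ANCOVA has 0.53, 0.57, 0.66 and 0.82 at ρ = 0, 0.3, 0.5 and 0.7. The difference detectable with 80% power is 1.32 SD unadjusted, and 1.19 SD (ρ = 0.5) or 0.98 SD (ρ = 0.7) with ANCOVA.

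**Simulation check** (20,000 trials at each ρ). ANCOVA power was 0.54, 0.58, 0.66 and 0.81 at ρ = 0, 0.3, 0.5 and 0.7. Change-score power was 0.32, 0.44, 0.56 and 0.78. At ρ = 0.5 the simulated variances were 0.157 (ANCOVA) and 0.196 (t-test), a ratio of 0.80, as the formula gives.

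The Wilcoxon route likewise uses no baseline. Its loss was not calculated.

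**The case against.** **The value tested is not stated.** A reader might infer that the plan compares raw on-treatment values and throws the baseline away. The article does not say so, and a two-group test on change from baseline is not excluded. This stands as a matter of reading. It does not rescue the stated method, because the change-score test is less precise than ANCOVA at every correlation examined, and less precise than the plain t-test below ρ = 0.5.

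**The sentence does not name these measures.** The short-term secondary outcomes listed are durations and survival. The Secondary objective speaks of critically low function and output, which may be a threshold and so fall under the chi-squared or Fisher rule. This stands and limits the point to measures analysed as continuous.

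**Nothing is biased.** A reader might infer that baseline imbalance enters the difference in full, or that the test is wrong. Neither follows. Under randomisation the unadjusted comparison is unbiased, its standard error already allows for chance imbalance, and the carry-over is only ρ times the imbalance. This stands: the issue is efficiency.

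**This is a feasibility pilot without a power target.** This also stands. A reader might infer that the definitive sample size is compromised. The article says only: "This number will also allow us to calculate a standard deviation which will be used in a sample size calculation for the full-scale trial". It does not say that echocardiographic or NICOM variances will be used, and SDs and correlations can be computed from the data whichever test is chosen.

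**Covariates are commonly left to an analysis plan that is not shown.** This stands only in part. Silence would be no finding, but the article states a specific test for these outcomes, and that choice can be assessed.

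**Conclusion.** The point holds in a limited form. The article fixes a valid but inefficient test for any haemodynamic or oxygenation measure that has a pre-treatment value and is analysed as continuous. The gain from adjustment is material at moderate or high correlation: about 20% less variance at 0.5 and 46% less at 0.7. It is negligible at 0.3 (3%) and becomes a loss of about 6% at zero. The documents do not show where these measures fall in that range, so the size is conditional on assumed correlations, although the arithmetic itself is firm.

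It would be wrong to extend the point to the main comparison. Time on iNO, time on invasive ventilation and the duration-type secondary outcomes have no baseline value and are unaffected. This is a modest but worthwhile improvement to secondary analyses.

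**What to change.** State, before unblinding, that for each continuous measure with a pre-treatment value the arm difference is estimated by ANCOVA with that value as covariate. For the scheduled 12 h and 24 h measurements, one linear mixed model with baseline, arm, time and arm × time may replace separate tests. Log-transform skewed measures instead of switching to a rank test. Report each estimate with its 95% confidence interval. Because NICOM is recorded continuously, define its baseline and on-treatment summary values. Keep the existing two-group tests for outcomes without a baseline.

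The cost is a few lines of analysis text and no extra data. ANCOVA uses one degree of freedom and loses a little precision if the correlation is below about 0.25. The mixed model estimates more parameters, which matters with 20 infants, so ANCOVA at each time point is the simpler choice if the model proves unstable.

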### Objectives

#### Primary objective

We hypothesize that intravenous milrinone used in conjunction with iNO results in the reduction in the time on iNO therapy and the time spent on invasive ventilation in infants ≥34 weeks gestation and ≥ 2000 g with a clinical and echocardiography diagnosis of PPHN.

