## Conclusion

### Significant savings for the health service

A positive outcome in this pilot study will pave the way for a definitive trial of the use of milrinone for the treatment of PPHN. Improving the response rate to iNO and reducing the time on iNO and mechanical ventilation will have substantial short and long-term benefits for the healthcare service. Reduced length of stay will significantly reduce hospital costs in the neonatal intensive care unit. In addition, iNO administration is expensive (up to €50 per hour). Milrinone is relatively cheap costing about €30 per patient. There is potential for substantial savings if the use of milrinone is successful in reducing time on iNO. The increasing cost of iNO may soon preclude its use in both developed and developing countries so this study is urgently needed.

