### A greater understanding of the pathophysiology of PPHN

PPHN is a common occurrence in neonates and leads to a major burden of illness, carries a significant mortality, a need for ECMO, and adverse neurodevelopmental outcome. There is poor appreciation of the physiologic determinants of PPHN and predictors of iNO response at presentation with up to 40% of infants not responding to iNO treatment. The echo and NICOM measurements performed in this study will provide evidence both on the pathophysiology of PPHN but also on the efficacy of milrinone therapy.

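### A pilot whose stated purpose is feasibility makes efficacy on two durations its primary objective and judges it at p < 0.05 with 10 infants per arm

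*Protocol article*

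**What the plan says.** **Purpose.** The section on the relevance of the primary outcome gives the purpose as feasibility of a pivotal trial and preliminary data for its sample size. It lists what is to be learned: recruitment and consent, compliance with the protocol, loss to follow-up, and acceptability. It adds: "This number will also allow us to calculate a standard deviation which will be used in a sample size calculation for the full-scale trial". The Sample size section repeats the feasibility purpose and sets the number without an effect size, SD or power: "A sample of 10 infants per arm (a total of 20 infants) will be recruited over a 4-year period".

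**Objective and outcome.** The Primary objective section states an efficacy hypothesis, that milrinone with iNO "results in the reduction in the time on iNO therapy and the time spent on invasive ventilation". The monitoring and outcomes section agrees: "The primary outcome of this study is the time on iNO in hours and the time on invasive ventilation". Practicality of the protocol and the contribution to a sample size appear only in the closing sentence of the Secondary objective section.

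**Analysis.** The Statistical methods section compares both durations by t-test or Wilcoxon rank sum test, gives tests for the secondary outcomes, and closes with "We will accept a *p* value of < 0.05 as significant". It does not say whether one or both primary comparisons must succeed.

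**Use of the result.** The Conclusion says "A positive outcome in this pilot study will pave the way for a definitive trial", and that the echocardiographic and cardiac output measurements "will provide evidence both on the pathophysiology of PPHN but also on the efficacy of milrinone therapy".

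**The concern.** A pilot's primary objective should be the question the pilot is built to answer. Here the stated purpose is one thing, and the objective, outcome and decision rule are another. The sample was chosen for feasibility and for estimating an SD, yet the headline analysis is a significance test of efficacy.

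The risk lies in interpretation. After four years of recruitment the natural headline would be whether p fell below 0.05. A non-significant result could be taken as evidence against milrinone when the trial could not have detected a moderate benefit. A significant result on one of two durations could be presented as success under a criterion nobody fixed beforehand. The feasibility findings, which the trial can deliver, would come second.

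**Working it through.** **1. The plan's own figure.** The only design figure is 20 infants, 10 per arm. There is no power calculation to reproduce. The effect sizes below are assumptions, shown as a range.

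**2. Power of the primary test.** Inputs: n = 10 per arm (Sample size section); significance level 0.05 (Statistical methods section), taken as two-sided because no sidedness is stated; normal data with equal variances. Degrees of freedom are 2 × 10 − 2 = 18, the critical t is 2.101, and the noncentrality is d × √(10/2) = 2.236 d, where d is the true difference in SD units.

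| Assumed d | Noncentrality | Power |
|---|---|---|
| 0.5 | 1.12 | 18.5% |
| 0.8 | 1.79 | 39.5% |
| 1.0 | 2.24 | 56.2% |
| 1.32 | 2.96 | 80% |

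The 95% confidence interval for a difference has half-width 2.101 × √(2/10) = 0.94 pooled SD. A non-significant result can therefore be compatible with a sizeable benefit, which an interval shows and a p-value hides.

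**3. Two primary durations.** If significance on either counts as success and there is no true effect:

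- independent outcomes: 1 − 0.95² = 9.75%
- correlation 0.5 (bivariate normal): 9.1%
- correlation 0.9: 7.0%

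If both must be significant, the error is at most 5%. These are two-sided rates and include results that favour placebo.

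**4. Precision of the pilot SD.** With a pooled SD on 18 df and normal data, the 95% limits as multiples of the estimate are √(18/31.53) = 0.76 and √(18/8.23) = 1.48. The required N varies with the square of the SD, so it ranges from 0.57 to 2.19 times the value from the point estimate. As an illustration at an assumed d = 0.5 and 80% power, the point estimate gives 2 × (1.960 + 0.842)² / 0.5² = 62.8, or 63 per arm. The limits give 62.8 × 0.571 = 35.9, or 36, and 62.8 × 2.187 = 137.3, or 138 per arm.

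**The case against.** **Low power is no fault in a pilot that claims none.** This stands. Twenty infants are justified by feasibility and SD estimation, and no section promises power. The figures matter only because the article attaches a significance rule to a primary efficacy objective.

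**The either-or-both rule may be settled elsewhere.** The primary hypothesis joins the two durations with the word and, which may mean that both are required. A separate analysis plan could also say so. This largely stands: the 7.0% to 9.75% applies only under the either reading.

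**Four stronger readings are tempting, and the article does not support them.**

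- *More than a hundred echocardiographic tests.* About 46 listed parameters at three post-baseline times would make 46 × 3 = 138 comparisons and, at 0.05, about 6.9 expected false positives. But the article says these parameters are collected, not that each is tested, and the secondary objective names only critically low ventricular function and output.
- *Progression decided by a p-value.* The phrase about a positive outcome is undefined and stands in the Conclusion. The section on the relevance of the primary outcome plans to seek funding for the next trial without any such condition.
- *A positive result would often be false.* The family-wise error is a chance under no effect, not the share of positive findings that are false. That share needs a prior. For one outcome at assumed even odds, counting only results favouring milrinone, it is 0.025/(0.025 + 0.395) = 6% at 0.8 SD and 0.025/(0.025 + 0.185) = 12% at 0.5 SD.
- *The SD will be used with no allowance for its imprecision.* The article says it will be used in a calculation and elsewhere that the pilot contributes to one. How a later trial inflates its planning SD is for that trial to decide, and conventions differ.

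The mismatch between the stated purpose and the primary objective with its significance rule remains. An analysis plan could not remove it without departing from the article's own text.

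**Conclusion.** The point holds as an internal inconsistency that should be corrected. The stated purpose is feasibility and planning, while the primary objective, the primary outcome and the criterion for judging results are about efficacy.

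A test at 10 per arm has roughly 19% to 40% power for assumed effects of 0.5 to 0.8 SD and reaches 80% only at about 1.32 SD. These figures assume a two-sided t-test on normal data. The durations may well be skewed, as the plan allows, so read them as orders of magnitude. The error rate over the two durations is 7.0% to 9.75% or at most 5%, depending on a rule the article does not state. The SD interval of 0.76 to 1.48 times the estimate also assumes normality. It shows how loosely this pilot can size the next trial; it is not evidence of an error in the plan.

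**What to change.** 1. Make the feasibility items already listed in the section on the relevance of the primary outcome (recruitment and consent, protocol compliance, loss to follow-up, acceptability) the primary objective.
2. In the Statistical methods section, replace the p < 0.05 rule with between-group differences and 95% confidence intervals. Label efficacy, secondary and echocardiographic results exploratory.
3. If a test is kept, name one primary duration or state that both must succeed.
4. Reword the two Conclusion sentences so that going on to a definitive trial rests on feasibility, not on a positive outcome or on evidence of efficacy.
5. Report the pilot SD with its confidence interval, and leave the degree of inflation to the definitive trial.

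The cost is wording only. Enrolment, treatment and data collection stay as they are. The downside is that the pilot can no longer report a significant efficacy result.
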